## Abstract

**Background:**

Mental health problems represent a large and growing public health concern. Primary care handles most of the patients with mental health problems, but there are many barriers to detection and treatment in this setting, causing under-recognition and under-treatment of patients. The service delivery model Primary Care Behavioral Health (PCBH) shows promise to manage mental health problems in primary care, but more research is needed regarding its effects on multiple levels.

**Methods:**

This project investigates the effectiveness and implementation of a large-scale implementation of PCBH in Region Östergötland, Sweden. The aim is to generate new knowledge concerning the impact of a real-world implementation and use of PCBH in routine primary care. A Pragmatic Stepped-Wedge Cluster Trial will be used: 24 PCBH primary care centres in one region will be compared with 48 standard care centres in three other regions. The model will be implemented sequentially at the PCBH centres according to a staggered timetable. Results will be investigated at patient, staff and organization levels and various forms of data will be collected: (1) local and national registry data; (2) questionnaire data; (3) interview data; and (4) document data.

**Discussion:**

This project investigates the effectiveness and implementation of PCBH in routine primary care. The project could result in improved mental health care for the included patients and contribute to the general good for a wider population who have mental health problems. The project’s study design will make it possible to assess many important effects of the PCBH service delivery model at different levels, providing evidence of the effectiveness (or not) of the PCBH model under routine conditions in primary care. The project has the potential to generate clinically meaningful results that can provide a basis for decisions concerning further implementation and use of the model and thus for future development of mental health care provision in primary care.

**Trial registration:**

NCT05633940, date of registration: 2021–04-21.

## Contributions to the literature

The project investigates the implementation of a comprehensive service delivery model, comparing 24 primary care centers implementing the model with 48 “standard care” centers, thereby contributing knowledge about real-world implementation.A multifaceted evaluation approach is employed to enable an investigation of three levels of the service delivery model, patient, staff and organization levels, thus adding knowledge for implementation science which typically focuses on the staff level.A rigorous Stepped-Wedge design is applied, which is not a common design in implementation science, but is appropriate when practical, logistical and resource constraints make it difficult to deliver an intervention en bloc.

## Background

### Introduction

Both mental health problems (e.g., sleep disturbances and stress) and psychiatric disorders (e.g., depression and anxiety disorders) are highly prevalent in today’s society [1–5]. There is a strong connection between detrimental behavioral patterns and decreased mental health. Approximately 25–50% of all patients in primary care worldwide have symptoms attributable to behavioral or mental health problems, with an increasing proportion of symptoms occurring over time [3, 5–7]. These problems restrict individuals’ ability to function, engage in daily activities and maintain social relationships, causing significant suffering for individuals and their families [1, 2]. There is also a well-established link between mental health problems and low quality of life as well as cardiovascular disease, e.g., myocardial infarction and stroke [8, 9].

In Sweden, primary care handles most patients with mental health problems, with 50% to 70% of patients diagnosed with psychiatric diseases being managed in this setting [2, 10]. The corresponding international figure is approximately 60% [7]. Despite the high prevalence of mental health problems, there are many barriers to achieving optimal detection and treatment in primary care [11]. Thus, mental and behavioral health problems represent a major challenge for already strained primary care, where the need for mental health care exceeds the available resources [1–5].

The majority of mental health problems present in primary care can be managed by psychological interventions or even self-care [10]. The recommended evidence-based treatment for mild to moderate mental health problems often is manualized cognitive behavioral therapy (CBT), which focuses on changing both patients’ thoughts and behavioral patterns [12]. However, very few primary care patients, both worldwide and in Sweden, receive CBT, primarily due to a lack of resources [1–3, 6, 13]. There is a shortage of psychotherapists, psychologists and nurses [14], which restricts care opportunities, often resulting in long waiting lists, delays and multiple, diverse contacts before appropriate care is obtained, which may lead to worsening symptoms that ultimately manifest as psychiatric disorders [10, 15, 16]. Another consequence is overmedication with psychotropic drugs [13].

### The primary care behavioral health model

The primary care behavioral health (PCBH) model has attracted considerable interest from primary care organizations both in Sweden and internationally as a promising model for addressing the challenges of behavioral and mental health problems in the primary care population [17–19]. The PCBH model is a team-based primary care approach for managing mental health problems and biopsychosocially influenced health conditions. The model’s main goal is to enhance the primary care team’s ability to manage and treat such problems/conditions, with resulting improvements in primary care services for the entire clinic population. An important premise is to address these problems early on, focusing on helping patients learn skills to improve their functioning before symptoms develop into disease and, for example,reduce their work capacity. To this end, patients must be offered proactive, timely and adequate treatment in primary care [10].

The PCBH model strives to reduce behavioral health problems, thereby promoting overall health in the general population [18]. This objective is aligned with the overarching goals of primary care in Sweden [20], making the model clinically attractive. PCBH can be described as a patient-centered service delivery model based on a multiprofessional team-based approach [17–19]. The PCBH service delivery model has two primary key features that distinguish it from how primary care providers traditionally handle mental health issues, as described below:Behavioral health consultants: PCBH emphasizes high accessibility to an on-site behavioral health consultant (BHC) as a routine part of the primary care clinic. This on-site BHC works closely with physicians and assists all staff members at the clinic in addressing mental and behavioral health issues. The BHC works as a generalist and an educator in behavioral health at the primary care center, working in a productive, accessible manner [17–19]. In Sweden, the role of BHC is typically as a psychologist or psychotherapist. The ambition is that patients with mental health problems, if needed, may receive an appointment with a BHC either directly or within a few days. Such appointments can be arranged at the patient’s first visit to the center or immediately after a visit to a physician.Brief interventions: Short, timely interventions are offered for mental health problems as soon as these problems affect a patient’s functioning rather than interventions solely based on diagnostic criteria for psychiatric diseases [18]. In clinical practice, these interventions are targeted evidence-based interventions and can be delivered via several different modalities, such as face-to-face on-site meetings or via the internet [21].

### Knowledge gaps

Despite its potential, many aspects of the PCBH model have not been investigated. There have been calls for robust, clinically relevant research on the model, focusing on clinical, financial and operational factors and addressing patient, staff and organization levels [17, 19]. Knowledge is needed concerning the effects of PCBH on clinically relevant patient outcomes in diverse primary care patient populations. It is also important to conduct research to investigate the feasibility of PCBH in smaller or middle-sized primary care centers where resources might be limited. Furthermore, the effects of the PCBH on staff and organization levels, e.g., the model’s impact on waiting lists and the number of patients who receive treatment for mental health problems, are also important to evaluate. Knowledge is also needed about the barriers and facilitators to implementing PCBH in primary care and the acceptability, appropriateness and feasibility of using the model as part of routine work. The costs of implementing and working according to the model and the cost-effectiveness of PCBH are other relevant areas to investigate. The research project described in this protocol paper aims to address the majority of these issues.

### Objectives

The project aim for this Pragmatic Stepped-Wedge Cluster Trial is to generate new knowledge concerning the impact of a real-world implementation of PCBH in routine primary care in Sweden. Twenty-four PCBH primary care centers will be compared with 48 standard care centers. The results will be investigated at the patient, staff and organization levels. Eight research questions (RQs) are addressed (for details, see Table 1):

**Table 1 Tab1:** Data sources and focus for each research question

Focus	Research question	Data source(s)
Patients	(RQ1) What are the effects of PCBH on patient outcomes compared to standard care?	• National registry data, INERA certification service (Swedish Social Insurance Agency): Patient sick leave due to mental health problems (i.e., sick leave due to ICD10: F00-F99, Z56, Z73F) • Local registry data: Referrals to secondary psychiatric care based on electronic medical records
	(RQ2) What characterizes patients who receive care according to the PCBH model compared to standard care?	Local registry data except where noted • Patient demography (gender, age) • Patient diagnoses F00-F99, Z56, Z73F according to ICD10, including specific diagnoses and combinations of diagnoses • Comorbidity calculated using the Charlson Comorbidity Index • National registry data, Swedish Prescribed Drug Registry national data (National Board of Health and Welfare): Medication with psychotropic drugs coded as N05A, N05B, N05C and N06A according to the ATC system
	(RQ3) How do patients experience the care provided at centers that implement PCBH?	• Interviews: Patient experiences with the behavioral consultant care they have received will be explored with interviews
Staff	(RQ4) How do health care staff members experience working with PCBH in terms of barriers to and facilitators for implementation?	• Interviews: Staff experiences of working with PCBH in terms of e.g., barriers and facilitators for implementation of PCBH in routine care
	(RQ5) How do mental health therapists’ experience their new PCBH-specific role as behavioral health consultants?	• Interviews: Mental health therapists’ experiences of taking on the new role as behavioral health consultants
	(RQ6) How does implementation of the PCBH model affect the work environment?	Questionnaires • Sociodemographic factors: age, gender, profession, year in that profession, time employed at the primary health care center • Staff psychosocial factors: the COPSOQ III questionnaire • Staff work commitment: Utrecht Work Engagement Scale • Exhaustion among co workers: KEDS
Organization	(RQ7) How does PCBH influence accessibility to mental health care in primary care?	All based on local registry data: • Organization and context characteristics: number of employees, number of behavioral health consultants and physicians, number of listed patients, characteristics of the catchment area, care need index (CNI) and adjusted clinical groups • Number of visits to behavioral health consultants • Waiting times to first visit and revisits to behavioral health consultants and physicians • Types of mental health interventions (e.g. focused acceptance and commitment therapy, motivational interviewing, concise CBT, behavioral activation) • Format of delivery (e.g. internet-based or self-help materials) • Number of visits to physicians for patients diagnosed with F00-F99, Z56, Z73F, or prescribed medication with N05A, N05B, N05C and N06A
Economy	(RQ8) What is the cost-effectiveness of implementing and working based on PCBH?	The cost analysis will be based on several data sources, including registry data also used to address RQ1 and written documentation concerning the implementation activities undertaken during the implementation period for each participating primary care center

*Abbreviations: PCBH* Primary care behavioral health, *RQ* Research Question

Patient level:(RQ1) What are the effects of PCBH on patient outcomes compared to standard care?(RQ2) What characterizes patients who receive care according to the PCBH model compared to standard care?(RQ3) How do patients experience the care provided at centers that implement PCBH?

Staff level:(RQ4) How do health care staff members experience working with PCBH in terms of barriers to and facilitators of implementation?(RQ5) How do mental health therapists' experience their new PCBH-specific role as behavioral health consultants?(RQ6) How does implementation of the PCBH model affect the work environment?

Organization level:(RQ7) How does PCBH influence accessibility to mental health care in primary care?(RQ8) What is the cost-effectiveness of implementing and working based on PCBH?

## Methods

### Study setting

This research project will study the real-world implementation of the PCBH in routine primary care in the Region Östergötland (RÖ), Sweden. The trial will include 24 intervention primary care centers (PCBH) and 48 control centers located in adjacent regions. Implementation sites will be matched with control sites based on the number of listed patients, number of employees (psychologist/psychotherapist and physicians), characteristics of the catchment area, care need index (CNI) and adjusted clinical groups (ACG). All participating sites are situated in southern Sweden in both urban and rural locations.

### Study design

The study is a Pragmatic Stepped-Wedge Cluster Trial, which enables us to study multiple effects on several different levels, encompassing both quantitative and qualitative methods. This design is increasingly used in the evaluation of service delivery models [22]. Pragmatic clinical trials evaluate interventions and service delivery models under real-life routine practice conditions [23]. In cluster trials, preexisting groups, in this case, primary care centers, are allocated to intervention or control groups [24]. In this stepped-wedge design, the model is implemented sequentially at the included centers according to a staggered timetable. Stepped-wedge trials are considered more powerful than traditional parallel studies when clusters are relatively heterogeneous and/or large [25], which is the case in this project. The control centers will be offered the model after the study period. We used the SPIRIT checklist when writing our report.

### Implementation of the model

There is a regional decision that PCBH should be implemented in the whole primary care in RÖ in the south-east region of Sweden, and the research group is working closely with the assigned regional implementation team, which consists of psychologists with special training in PCBH.

The implementation process will be carried out according to the Swedish Public Health Agency’s “Checklist for implementation with quality” [26]. 1) Initial assessment of needs and resources; 2) structure for implementation; 3) actual implementation; and 4) learn and improve. For each primary health care center, an initial assessment of needs and resources take place, followed by an individually tailored structure for implementation. When implementation starts, all medical staff receive a PCBH education for 1–4 days depending on the profession (e.g., 4 days: staff categories who will take on the role of on-site behavioral health consultants, typically psychologists and psychotherapists; 2 days: nurses; 1 day: physicians). Thereafter, tutoring sessions per profession are being carried out approximately once/month, more often if needed, to promote retention of the PCBH model. The active implementation period for each intervention center is approximately 12 months, during which scheduled lectures and workshops, continuous on-demand support, materials and instructions are provided by the implementation team. Thereafter, further support for maintenance will be offered by the implementation group for at least 24 months according to the needs of each center. All the implementation activities are endorsed and funded by RÖ. See also Fig. 1: SPIRIT flow diagram.

**Fig. 1 Fig1:**
[figure not shown]
SPIRIT flow diagram. Legends: SPIRIT flow diagram for enrolment, interventions, and assessments. For details regarding assessment and outcome variables, see Table 1

### Logic model

A logic model was developed by the research team to describe the project and enable reflection on the assumptions underlying the implementation of the PCBH service delivery model in RÖ; see Fig. 2. The logic model provides information about the problems addressed by the PCBH model and graphically depicts the relationships between the PCBH activities, the strategies used to support the implementation of the model and the various intended outcomes. A logic model is a systematic and visual way to present and share hypothesized descriptions of the chain of causes and effects leading to outcomes of interest of an intervention [27].

**Fig. 2 Fig2:**
[figure not shown]
Logic model. Legends: Logic model for the research project, which depicts the relationships between the PCBH activities, the strategies used to support the implementation of the model and the various intended outcomes. Abbreviations: PCBH: primary care behavioral health

First, the logic model identifies the three key problems of the poor current state of behavioral health in primary care globally: problems that the PCBH model is intended to solve or reduce; 1) insufficient knowledge concerning behavioral health care among the primary care staff; 2) poor patient access to relevant behavioral health care; and 3) high work demands for primary care staff that make it difficult to handle behavioral health issues in busy clinical reality [1–3, 6, 13, 28, 29]. These problems are described as the “starting conditions” of the PCBH model.

The “input” in the logic model is provided by the intervention, i.e., the PCBH service delivery model, and the implementation strategies that will be used to facilitate its implementation in routine primary care. The PCBH model and detailed implementation strategies are described elsewhere in the study protocol.

The following four types of “outcomes” are delineated in the logic model: staff, implementation, service and patient outcomes. Implementation, service and patient outcomes are informed by an implementation outcome taxonomy developed by Proctor et al. [30], while staff outcomes are based on insights about the PCBH model, as conveyed in the literature on the model [17–19].

Staff outcomes are intended effects pertaining to the staff in the primary care centers that implement the PCBH model, e.g., improvements with regard to staff members’ self-efficacy in working with behavioral health issues, work environment and better interprofessional collaboration. Implementation outcomes relate to various aspects of the implementation of the PCBH model, e.g., cost and fidelity. Service outcomes are related to desirable service-level effects if the PCBH services are delivered to the expected standard. These effects include the model’s intended improvements in, e.g., accessibility to care and timeliness of receiving care compared to standard care. Patient outcomes are the desired patient effects of receiving care according to the PCBH model. Compared to standard care, the PCBH model is intended to achieve increased patient satisfaction, reduced sick leave, less prescription of medication and fewer referrals to secondary care.

### Participants

#### Primary care center recruitment

Four pilot primary care centers have already been enrolled in the project, to test the protocol. After this pilot enrollment and adjustments of the implementation procedure, the protocol was adjusted to the final version. Following the pilot implementation of PCBH, a total of 24 primary care centers in RÖ will be enrolled in the research project (representing a total of 70% of all centers in this region). According to a staggered timetable, eight centers will be included in Year 1, eight in Year 2 and eight in Year 3, for a total of 24 centers over a three-year period. These 24 primary care centers in RÖ will be matched with 48 control centers from adjacent county councils in Jönköping, Kalmar and Örebro. Matching will be based on the number of listed patients, number of employees, number of behavioral health consultants and physicians and characteristics of the catchment area (CNI and ACG). A similar cluster-based approach has previously been used in research conducted at Linköping University [31].

#### Patient recruitment

The eligible study participants are all adult patients (≥ 18 years) who have either received any of the following International classification of disease (ICD)-diagnoses: F00-F99 (mental and behavioral disorders) or Z56 (problems related to employment) or Z73 (problems related to life-management difficulties) at a visit to a physician or a behavioral health consultant or are prescribed any psychotropic drug (Anatomical Therapeutic Chemical (ATC) codes: N05A-C, N06A) at a participating center. These patients will be identified through their medical records. In addition, a purposive sample of patients (approximately 20) at the intervention centers will be invited to participate in interviews regarding their experience and satisfaction with care. Sampling will aim for maximum likelihood variation based on, e.g., age, sex, and education.

#### Staff recruitment

Purposive samples of health care professionals working at PCBH centers will be invited to participate in a series of interviews, e.g., about their experience working with PCBH. Sampling will aim for maximum likelihood variation based on, e.g., the center and years in practice. We estimate that approximately 15–20 interviews for each study will be sufficient to capture the study aims, as all informants will have experience with PCBH and its implementation.

#### Data collection and analysis

Various forms of data will be collected to study the three levels, patients, staff and organizations: (1) local and national registry data; (2) questionnaire data; (3) interview data; and (4) document data. Data will be stored in a pass-word protected server. All records that contain names or other personal identifiers will be stored on a similar pass-word protected server, separately from study records identified by code number. All the data analyses will be performed on pseudonymized data. The principal investigator for the study will have access to all data. Other mandated researchers within the research group will have access to pseudonymized data. A brief summary and discussion of each research question follow; see also Table 1 for the listed data sources.

##### RQ1: Effects of PCBH on patient outcomes

 National registry data on sickness absence and local registry data concerning referrals to secondary psychiatric care will be used to assess the effects of PCBH compared to standard care. Mental health problems are well documented as an important cause of sick leave, underscoring the relevance of using sick leave as a hard endpoint. Referral to secondary psychiatric care is relevant for investigating whether early PCBH-based interventions for mental health problems lower the risk of developing more severe problems due to psychiatric disorders. The effects of PCBH in terms of changes in sick leave and referral to secondary psychiatric care will be measured in the year prior to and the years after PCBH implementation. Rates for referral will be calculated using the number of visits due to mental health problems in the primary care setting and the number of patients referred to additional services in secondary psychiatric care. Data pertaining to sick leave will be obtained from registries from the Swedish Social Insurance Agency, concerning patient sick leave due to mental health problems (i.e., sick leave due to ICD10: F00-F99, Z56, Z73F). For the number of referrals, local registry data in the form of electronic medical records will be used.

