#### Sample size

Approximately 3% of all patients in primary care receive an intervention by a behavioral health consultant [6, 13]. We hypothesize that this number will be at least 50% higher in the intervention group compared to the control group. A sample size based on a 50% increase, a power of 0.8 and a significance level of 0.05 yields a minimum of 1983 participants per group. Since we are using a design where heterogeneity of the populations and primary care centers probably will reduce the likelihood to detect meaningful changes, it is reasonable to double the number of participants to 3966 individuals per group. One of the pilot primary care centers has 14,841 listed patients. A study regarding Swedish primary care showed that approximately 66% of the population receives care annually at a primary care center [5]. It can thus be estimated that 9,795 (14,841 × 0.66) individual patients receive care annually at this center. If we assume that 3% [6, 13] of these patients receive a behavioral health consultant intervention, approximately 294 (9,795 × 0.03) patients annually receive a PCBH-based intervention. After the implementation of the PCBH delivery model, we estimate that this number will increase to 441 individual patients per year for one single primary care center (i.e., a 50% increase in the intervention group: 294 × 1,5 = 441). Since the project will involve 24 primary care centers, the requested sample size of at least 3966 individuals will not pose any difficulties, even considering that the number of listed patients among these centers ranges from approximately 4,500 to 21,500 listed patients (in December 2022). It should be noted that it is difficult to estimate the power of cluster studies because there can be heterogeneity within and between clusters.

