## Pilot study

The first 4 pilot centers that implemented PCHB have undergone some preliminary analyses to investigate feasibility of the project. The preliminary results are promising; in 3 of the 4 centers, the waiting lists to receive mental health care disappeared, and waiting times for visits for mental health problems decreased from 24.2 to 4.7 days (first visit) and from 22.5 to 6 days (revisits). At all the pilot centers, the number of patients who received care for mental health problems increased (a mean increase of 78%, range: 11–194%). The majority of the primary care staff at the pilot centers believed patients’ mental health care had improved and that their work had been facilitated by the implementation of PCBH, and 103 patients at the pilot centers reported being satisfied or very satisfied with the received care in a questionnaire on patient satisfaction.

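### The RQ1 referral rate uses mental-health visits, which PCBH is meant to change, as its denominator, so it can fall with no change in the number of people referred

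*Protocol article*

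**What the plan says.** Under RQ1 (Effects of PCBH on patient outcomes) the protocol article builds the referral outcome from two counts. One, the natural numerator, is "the number of patients referred to additional services in secondary psychiatric care". The other is a count of primary care contacts, not of people: "Rates for referral will be calculated using the number of visits due to mental health problems in the primary care setting". It names no other denominator. Table 1 lists referrals to secondary psychiatric care as one of two RQ1 outcomes, the other being sick leave, and gives no denominator for them.

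The same section gives the purpose of the outcome: to see whether early PCBH-based interventions "lower the risk of developing more severe problems due to psychiatric disorders". Changes "will be measured in the year prior to and the years after PCBH implementation". The Logic model section lists the intended patient effects as including "reduced sick leave, less prescription of medication and fewer referrals to secondary care".

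Elsewhere the article expects PCBH to expand mental-health care:

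- **Sample size**, on patients who receive a behavioral health consultant intervention: "We hypothesize that this number will be at least 50% higher in the intervention group compared to the control group".
- **Pilot study**, on the four pilot centres: "the number of patients who received care for mental health problems increased (a mean increase of 78%, range: 11–194" per cent).
- **Table 1 and the RQ7 section** list visits to consultants, and physician visits by patients with the relevant diagnoses or prescriptions, as accessibility outcomes.

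**The concern.** A rate is a fair measure of effect only if the intervention leaves its denominator alone. Here the denominator is a count that PCBH sets out to change, through quick access to a consultant and brief interventions offered before diagnostic criteria are met. Extra visits for milder problems lower the ratio even if nobody avoids a referral. The comparison with control centres does not remove this, because those centres have no PCBH-driven change in visits.

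The units also differ: the numerator counts patients and the denominator counts visits. A change in revisits per patient therefore moves the rate by itself.

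What is at stake is one of the two RQ1 effect outcomes. Better access could be reported as prevention of more severe illness, in a project meant to inform decisions on wider implementation.

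**Working it through.** **The plan's own figures.** The article states no expected referral rate and no expected change in total mental-health visits. It does give a volume calculation for one pilot centre (Sample size), which reproduces: 14,841 × 0.66 = 9,795 patients seen per year; 9,795 × 0.03 = 294 consultant patients; 294 × 1.5 = 441 under PCBH.

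**Formula.** Let R be patients referred and V mental-health visits before implementation. If R is unchanged and V becomes mV, then

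rate ratio = (R / mV) / (R / V) = 1/m.

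If control-centre visits stay level, the between-group contrast is shifted by the same 1/m.

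**Illustrations, assuming that visits rise in proportion to the quoted patient increases:**

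| Source of the increase | m | Rate ratio 1/m | Fall in rate |
|---|---|---|---|
| Pilot, lowest centre (+11%) | 1.11 | 0.90 | 10% |
| Sample-size hypothesis (+50%) | 1.50 | 0.67 | 33% |
| Pilot mean (+78%) | 1.78 | 0.56 | 44% |
| Pilot, highest centre (+194%) | 2.94 | 0.34 | 66% |

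**Why m is uncertain.** The 50% figure counts consultant patients only, and the 78% figure counts patients, not visits. The denominator is all mental-health visits, and the article counts both physician and consultant visits for these patients. Let s be the share of visits made to consultants (assumed; not in the article).

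- Consultant visits +50%, physician visits unchanged: m = 1 + 0.5s. For s = 0.2, 0.5 and 1.0, m = 1.10, 1.25 and 1.50, and the rate falls by 9%, 20% and 33%.
- s = 0.3, consultant visits +50%, physician visits −20%: m = 0.3 × 1.5 + 0.7 × 0.8 = 0.45 + 0.56 = 1.01, and the fall is about 1%.

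Conversely, for a 78% rise in patients to leave total visits unchanged, visits per patient would have to fall by 1 − 1/1.78 = 44% (33% for a 50% rise). The article predicts no such fall.

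**Effect of changing the denominator.** Assume, for illustration, 15 patients referred per year at the example centre both before and after. Per 1,000 listed patients the rate is 15 / 14,841 = 1.01 both times, a ratio of 1.00. Using the article's consultant-patient volume as a stand-in for a denominator that PCBH moves, it goes from 15/294 = 5.1% to 15/441 = 3.4%, a ratio of 0.67.

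**The case against.** The strongest reply concerns size. The quoted increases are not increases in visits, the pilot figures come from four centres with no control reported, and work moved from physicians to consultants could leave total visits almost unchanged. This stands: the percentages are scenarios and not forecasts. It does not rescue the rate, whose meaning would then depend on an offset that the article neither predicts nor controls for.

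A second reply is that the components are visible. Referral counts are collected, visits are reported under RQ7, and list size is to be accounted for in the analyses (Statistical considerations). This also stands in part. A reader might infer that the rate would hide a rise in referrals. Arithmetically, at m = 1.78 referred patients could increase by up to 78% before the rate rose, but the raw counts would show it. Having the counts, or adjusting for list size, does not however correct a denominator that the intervention itself has changed.

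A third reply is that referrals per visit is a legitimate measure. It is one of referral propensity per contact, but that is not the risk named in the RQ1 section. Nor is a population rate neutral in every respect: better detection under PCBH could raise referrals per listed person without anyone's condition worsening.

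Finally, the wording is loose (calculated using, not divided by) and sits in a condensed article, and a full protocol or SAP may define the rate more exactly. But the article does state a construction, and visits as the denominator is its natural reading.

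**Conclusion.** The concern holds. As written, the RQ1 referral rate can fall by a factor of 1/m with no referral prevented, and it mixes patients with visits. By itself it cannot support a conclusion of fewer referrals or of a lower risk of more severe problems. The direction of the distortion rests on total mental-health visits rising under PCBH, which the model's aims and the pilot make plausible. Its size is unknown because the article gives no m for total visits. Falls of 10% to 66% apply only if visits follow the quoted patient increases; with partial substitution the fall could be near zero.

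A reader might go further and infer that a statistically significant reduction is almost guaranteed. The article does not support that: significance depends on the baseline referral rate, the between-centre variation and m, and it gives none of these.

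**What to change.** Define the RQ1 referral outcome as the number of unique patients referred to secondary psychiatric care per 1,000 listed patients, per centre per year. Use listed adults if the age breakdown can be obtained, since eligibility is limited to adults. Enter list size as the offset in the multilevel model. Report mental-health visits under RQ7, and keep referrals per visit as a secondary, descriptive measure of referral propensity. Patients seen for mental health problems would not be an adequate denominator, because PCBH is expected to raise that count too.

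The cost is about one sentence in the protocol or SAP. Listed patients per centre are already collected; the adult breakdown would be an extra request. There are two drawbacks. The rate is numerically small, and improved detection may raise population referrals, which should be noted in advance as a point of interpretation.
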